### Recruitment and data collection procedures

In each study center, a trained study assistant will identify potentially eligible infants and inform the parents about the study both verbally and via printed information material. Interested parents will receive the information material and a copy of the informed consent form to read. A member of the research team will answer any parental questions about the study. No study procedures will be performed until a signed informed consent form is obtained from the child’s parents.

After written consent has been received, the neonate will be videotaped (using a HC-V757 high-definition camcorder manufactured by Panasonic, Osaka, Japan) during his or her next 2–5 routine capillary heel sticks. Before each heel stick procedure, every infant will receive a dose of 24% oral sucrose (0.2 ml/kg bodyweight) as a pain relieving intervention in accordance with standards of care [66]. Video sequences and physiological variables will be recorded continuously from 2 to 3 min before the beginning of the heel stick procedure (baseline phase), through the heel stick (heel stick phase) and until 2–3 min after the heel stick (recovery phase). Therefore, three rating sequences will be produced for each heel stick. The camera operator will begin each video sequence by focusing on the face of the neonate for at least one minute to allow adequate assessment of facial activity and cry. Then, the infant’s body will be recorded for another minute. For healthy-term infants, six video sequences per infant will be produced, resulting in 96 videos (2 heel sticks * 3 phases * 16 n). For premature neonates, 2010 video sequences (5 heel sticks * 3 phases * 134 n) will be produced. This will lead to a total of 2106 video sequences, all of which will be filmed by trained study collaborators. Each video sequence will be checked for quality, and digitally elaborated by trained study assistants using Final Cut Pro X (Apple Inc., Cupertino, CA, USA) video editing software. To preserve rater blindness, any information that could indicate the heel stick phase to the raters will be eliminated. Data quality and completeness of the video sequences will be controlled continuously by the doctoral student before uploading each video sequence onto a web-based rating tool. The web-based rating tool has been developed specially for the study and includes a randomizing generator. Uploaded sequences are randomized related to sequence number, phases and presentation order. Five trained nurses who are presently working in a NICU and are experienced users of the BPSN will retrieve the randomized sequences from the web-based platform and will rate the behavioral pain reaction by means of the BPSN and the PIPP-R.

Individual contextual factors will be retrieved retrospectively from patient charts by trained study assistants. All extracted data will be entered into secuTrial®, a web-based data capture system (InterActive Systems, Berlin, Germany). Five percent of the patient charts will be audited by the doctoral student to detect and correct discrepancies. Emerging questions and inconsistencies during the overall data collection process will be continuously discussed to ensure the quality of ongoing data extraction.

### Measures

To establish concurrent validity, neonates’ pain expression is measured by the BPSN [41] and the PIPP-R [26]. The BPSN measures 9 indicators. The two physiological indicators will be captured on an ongoing basis from the neonate’s routine continuous monitoring records (heart rate and oxygen saturation) during the video recording. The six subjective indicators (sleeping state, crying, consolation, skin color, facial expression, posture, and breathing) will be rated by five independent and blinded video raters on a 4 point Likert scale. The raters are blinded towards the phase of the video sequence they are looking at (baseline, heel stick, and recovery). The PIPP-R, which is widely used in North America for assessing acute pain in neonates, measures five indicators of which two are physiological (heart rate and oxygen saturation). The three behavioral indicators (brow bulge, eye squeeze, and naso-labial furrow) will also be assessed by the five raters. Each indicator of the PIPP-R is numerically rated on a Likert scale from 0 to 3 points, with higher ratings reflecting the rater’s impression of more intense pain responses. Additionally, the PIPP-R accounts for GA and baseline behavioral states as contextual factors. According to the instructions of the authors, these contextual factors need only be scored if there are changes in any of the behavioral or physiological items [26]. Neonates with the youngest GAs and those in quiet sleep receive the highest scores for these indicators. The PIPP-R scores will be used as a standard reference in this study.

Based on the findings of a systematic review [44], the following individual contextual factors will be retrieved from patient charts: demographic contextual factors, including GA at birth, gender, birth weight, nationality, parity and way of delivery; the primary diagnosis and the most common comorbidities in preterm neonates, including bronchopulmonary dysplasia, necrotizing enterocolitis, respiratory distress syndrome, patent ductus arteriosus, septic events, cardiac events and respiratory events; the health status at time of birth measured by the Clinical Risk Index for Babies (CRIB; [67]). For the time of each heel stick, the following individual contextual factors will be retrieved: postnatal age; post-menstrual age (GA at birth combined with postnatal age); weight; CPAP or mechanical ventilation at the time of the heel stick procedure; medication administered (sedatives, opioids, non-opioids, steroids, caffeine, antibiotics and catecholamines) from birth and between the recorded heel stick procedures; number of previous painful (e.g., heel stick) and non-painful (e.g., diaper change) interventions from birth and between the recorded heel stick procedures (painful and non-painful interventions were defined in a previous study [68]); number of painful and non-painful procedures in the past 24 h; time since the last painful and non-painful interventions; and, finally, type of last painful and non-painful interventions. The duration of each heel stick and the number of additional sucrose doses given during the heel stick procedures will be registered while video recording.

### Data analyses

Data will be analyzed using SPSS (IBM© SPSS© Statistics Version 23.0, IBM Corp, Armonk, NY, USA) and Stata (Stata/MP 13.1, StataCorp LP, [name], USA). Initially, an exploratory analysis will be conducted to describe the data and uncover any anomalies that may impact the validity of the data analysis. Methods for handling missing data will be applied after considering the volume and pattern of missing data. Descriptive statistics including measures of central tendency and dispersion will be used to characterize the individual variables and to determine the distribution of the data.

Several data analyses will be used for the validation of the BPSN. An exploratory factor analysis will be performed to analyze the underlying structure of the data. Cronbach’s Alpha and item-total correlations will be conducted to analyze the reliability of the scale. Furthermore, construct validity will be examined by comparing mean measurements at each of the three rated phases (baseline, heel stick and recovery). The analysis will be performed for the total sum score of the BPSN as well as for the physiological items and the behavioral items alone. In order to determine the concurrent validity of the BPSN with the PIPP-R, the total sum scores of the two tools will be correlated. Intra-class correlation (ICC) will be used to determine interrater reliability across the 2–5 heel sticks. To test sensitivity and specificity in the BPSN, a receiver operating characteristic (ROC) curve analysis will be performed using the PIPP-R as reference value. Furthermore, the pain and non-pain cut-off values of the two instruments will be compared.

To explore and depict both temporal variability of pain reactivity between measurements of each subject, and variability between corresponding measurements of all subjects, linear mixed modeling will be applied to the behavioral and physiological data on pain reactivity. Additionally, individual contextual factors will be added to these models to test for associations with the BPSN scores. As contextual factors are highly dependent on organizational procedures, the possible confounding effect of the participating sites will also be taken into account.

In addition to analyzing the total sum scores of the BPSN, the separate physiological and behavioral subscores will be tested both against the total scores and against one another. Pearson correlation will be used as a descriptive indication of the strength of associations, while linear mixed modeling will be used to test the associations themselves.

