### Pain assessment in neonates

Clinical pain assessment in neonates, particularly those delivered preterm, is highly challenging [4, 23]. In the clinical setting, their pain responses have to be observed and assessed using behavioral and physiological indicators, which can vary across premature infants depending on their physiological and neurological development stages [23]. Behavioral indicators used as pain assessment tools include body movements, facial expressions and crying [24]. Some pain assessments also include behavior status indicators, e.g., sleep-wake state [25, 26]. Physiological responses to pain include, for instance, changes in heart rate, respiratory rate, blood pressure, oxygen saturation, vagal tone, and peripheral blood flow [25, 27]. Recently, researchers have begun to investigate more objective approaches to pain assessment, such as measurement of heart rate variability, skin conductance and cortisol as a biomarker of stress [23, 25]. To better understand and assess neonatal pain responses at cortical level, newer brain-oriented techniques, such as electroencephalography (EEG) [28, 29] and functional magnetic resonance imaging (fMRI) [30, 31], are used [11, 32–34]. However, for systematic clinical pain assessment, exclusively observable indicators need to be considered.

Because of the complex nature of pain, multidimensional pain measures that include behavioral and physiological indicators are generally assumed to be most appropriate for the clinical setting [23]. Although most infants show both types of pain response indicators, the correlation between these two indicators is often low [25, 35]. Moreover, no consistent associations between behavioral, physiological and cortical measures of pain have been detected so far [36]. In the face of inconclusive associations between different indicators of pain, the validity of existing multidimensional tools and their choices of indicators are currently being questioned, and, to date, no universally accepted gold standard exists for neonatal pain assessment [23].

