### The Bernese pain scale for neonates

The Bernese Pain Scale for Neonates (BPSN; [41]) was developed by nurses of the University Hospital of Berne primarily for clinical use. Since its development in 1996, it has been widely used for bedside pain assessment in NICUs in the German speaking areas of Europe. Several hospitals in Switzerland have fully integrated the BPSN into their daily routine.

The BPSN is a 9-item multidimensional pain assessment tool that includes behavioral and physiological indicators. The instrument consists of seven subjective (alertness, crying, consolation, skin color, facial expression, posture, and changes in respiratory rate) and two physiological (i.e. objective) (changes in heart rate and oxygen saturation) indicators. Each item is rated on a four point Likert scale (0, 1, 2, and 3). Higher scores indicate greater pain-related distress, and a total score of 11 or higher is considered to indicate pain.

In the year 2004, the BPSN was validated to differentiate between pain and non-pain status in neonates between 27 and 41 weeks of gestation [41]. The results suggested that the BPSN is a valid and reliable pain assessment instrument for assessing acute pain in term and preterm neonates. A shortcoming of this first validation study of the BPSN is the small study population of 12 infants. Furthermore, increasing evidence indicates that pain reactions of neonates are probably influenced by more than noxious stimulation alone; individual contextual factors might also impact pain reactivity [40, 42–44]. Currently, the BPSN focuses entirely on physiological and behavioral indicators.

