### Study aims

The aim of this observation study is the validation of the BPSN, using a large sample of neonates spanning a full range of GAs. The validation will involve the detection of the underlying structure of the data and the examination of the concurrent validity of the BPSN with the Premature Infant Pain Profile-Revised (PIPP-R; [26]), construct validity, interrater reliability, specificity and sensitivity. Furthermore, the variability of pain reactions over time related to behavioral and physiological patterns will be analyzed and the relationship between behavioral and physiological indicators examined. In addition, the influence of contextual factors on the variability of pain reactions across GA groups will be explored. Finally, the results of this analysis will be used for modification of the BPSN, to account for individual contextual factors in future clinical pain assessment in neonates.

Based on a previous validation study of the BPSN [41], we hypothesize that the BPSN will be a valid and reliable pain assessment tool for premature and term infants. In addition, we expect that the impact of single contextual factors on infants’ pain reaction will be described and considered for future pain assessment. In particular, we anticipate finding a difference in pain reaction depending on GA. Moreover, we hypothesize that behavioral and physiological indicators will show low association across time and that this low association may be explained by the influence of individual contextual factors.

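### Alpha and item-total correlations are planned for the whole nine-item BPSN although its two domains are expected to be weakly related; report them by domain, with stratified alpha for the total

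*Protocol article*

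**What the plan says.** The scale is described in the section on the Bernese pain scale: "The BPSN is a 9-item multidimensional pain assessment tool that includes behavioral and physiological indicators". Seven items are subjective; the rest are "two physiological (i.e. objective) (changes in heart rate and oxygen saturation) indicators".

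For internal consistency, the Data analyses section names Cronbach's alpha and states that "item-total correlations will be conducted to analyze the reliability of the scale". It refers to the scale as a whole and does not mention domains.

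The Study aims hypothesise that the BPSN will be valid and reliable. They also say: "we hypothesize that behavioral and physiological indicators will show low association across time". The Background (Pain assessment in neonates) reports from the literature that "the correlation between these two indicators is often low", while also noting that "multidimensional pain measures that include behavioral and physiological indicators are generally assumed to be most appropriate for the clinical setting".

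Related analyses in the same section are:
- a factor analysis: "An exploratory factor analysis will be performed to analyze the underlying structure of the data";
- a comparison of the three phases for the total score, "as well as for the physiological items and the behavioral items alone";
- an ICC for interrater reliability;
- tests of the two subscores against the total and against each other.

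The article gives no acceptable value for alpha or for an item-total correlation, and no rule for removing items. It does not say which phases, heel sticks or raters enter these statistics.

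**The concern.** Alpha and item-total correlations of a summed scale are easiest to interpret when all items reflect one quantity. Here the plan itself expects two weakly related groups of unequal size. The corrected item-total correlation of heart rate is its correlation with a sum of seven rater-scored items and only one other physiological item. If the groups are weakly related, that value is low even when heart rate is measured well. The statistic then cannot distinguish a poor item from a correct hypothesis.

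What is at stake is interpretation. A validation report showing low item-total correlations for heart rate and saturation, and a higher alpha without them, could be read as evidence against including physiological items. The Background defends including them.

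**Working it through.** The article prints no alpha, item-total correlation or inter-item correlation, so there is no figure to reproduce. The check is a model with stated assumptions.

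**Inputs from the article.** Nine items: seven subjective, two physiological. (The Measures section counts six subjective items but names seven; seven is used here.)

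**Assumptions.** Equal item SDs; mean inter-item correlation 0.4 among the seven and 0.3 between the two; cross-domain item correlation c from 0 to 0.10.

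**Variances of sums of standardised items.**
- Seven subjective items: 7 + 42 × 0.4 = 23.8.
- Two physiological items: 2 + 2 × 0.3 = 2.6.
- Nine-item total: V = 23.8 + 2.6 + 28c, which is 26.4 at c = 0 and 29.2 at c = 0.10.

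**Alpha** = k/(k−1) × (1 − k/V).
- Nine items: 9/8 × (1 − 9/26.4) = 0.74; 9/8 × (1 − 9/29.2) = 0.78.
- Seven items: 7/6 × (1 − 7/23.8) = 0.82.
- Two items: 2 × (1 − 2/2.6) = 0.46.

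**Stratified alpha** = 1 − Σ V_i(1 − alpha_i)/V. The numerator is 23.8 × 0.1765 + 2.6 × 0.5385 = 4.2 + 1.4 = 5.6.
- c = 0: 1 − 5.6/26.4 = 0.79.
- c = 0.10: 1 − 5.6/29.2 = 0.81.
- Excess over ordinary alpha: about 0.05 and 0.03.

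**Corrected item-total correlation of a physiological item** = (7c + 0.3)/√(variance of the other eight), where that variance is 23.8 + 1 + 14c.
- c = 0: 0.3/√24.8 = 0.06.
- c = 0.10: 1.0/√26.2 = 0.20.

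**The same for a subjective item** = (6 × 0.4 + 2c)/√(7 + 30 × 0.4 − 1 + 2.6 + 24c − c-free terms), which simplifies to (2.4 + 2c)/√(20.6 + 24c), since six subjective items give 6 + 30 × 0.4 = 18 and the two physiological items give 2.6.
- c = 0: 2.4/√20.6 = 0.53.
- c = 0.10: 2.6/√23.0 = 0.54.

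**Other within-domain assumptions.** With 0.3–0.7 among subjective items, 0.1–0.5 between the physiological items and c from 0 to 0.10, the physiological item-total correlation is 0.02–0.26 and the subjective one 0.42–0.78. Dropping one physiological item leaves alpha unchanged or raises it, by up to about 0.04. Nine-item alpha is 0.66–0.89, mostly above 0.70.

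**Where the effect fades.**
- *Larger c.* Over the same ranges, the physiological item-total correlation is 0.18–0.33 at c = 0.15, 0.24–0.39 at c = 0.20 and 0.34–0.52 at c = 0.30.
- *Pooling phases.* Take within-phase correlations of 0.5, 0.3 and 0.05. The within-phase item-total correlation is 0.65/√29.7 = 0.12. If every item rises by d SD in the heel stick phase only, pooling three equal phases adds (1/3)(2/3)d² to every variance and covariance. At d = 1 (0.222 added): 2.43/√(1.222 × 43.9) = 0.33. At d = 1.5 (0.5 added): 4.65/√(1.5 × 61.7) = 0.48.

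**The case against.** The plan does not ignore structure. A factor analysis is announced immediately before alpha and would be expected to show a two-domain pattern. The subscores are tested against each other, and an ICC is planned, so reliability does not rest on alpha alone. A low physiological item-total correlation would also agree with the authors' own hypothesis, so they have reason to read it correctly. Reporting by domain is a detail that a condensed article may leave elsewhere, and nothing in the text rules it out.

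Much of this stands, and it excludes three stronger readings that a reader might infer:
- *That the physiological items must look poor whenever the association hypothesis is right.* The article gives no value for a low association. At c of about 0.20 or more, or with pooled phases, the item-total correlations are no longer very low.
- *That the items would be flagged or removed.* No cut-off or deletion rule exists, and the stated purpose of modifying the BPSN is to account for contextual factors.
- *That the reliability hypothesis and the low-association hypothesis contradict each other.* Nine-item alpha usually stays above 0.70 in the scenarios, so both could be observed.

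What the objection does not remove is that these analyses leave the planned statistics as they are. The factor analysis describes structure, but no sentence ties the reading of alpha to it. The sentence on each domain alone follows the phase comparison and does not clearly extend to alpha. The ICC concerns agreement between raters, whereas heart rate and saturation come from monitor records. The subscore tests concern association between domains, not consistency within them.

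**Conclusion.** The point holds in a limited form. Whole-scale alpha and item-total correlations are a weak choice for a scale expected to contain two weakly related domains. With a within-phase cross-domain item correlation of about 0.10 or less, low item-total correlations for heart rate and saturation would follow from structure and would not by themselves show poor measurement. Ordinary alpha would understate the reliability of the total by about 0.03–0.05 in the illustrative scenario, which is small and conservative.

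These sizes rest on assumed correlations and equal item SDs, since the article gives neither. The comparison with stratified alpha also treats what is consistent within each domain as true score. No planned figure or decision is shown to be wrong; this is a worthwhile improvement to analysis and interpretation.

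**What to change.** In the Data analyses section:

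1. State that alpha and item-total correlations will be read in light of the factor analysis.
2. Report them by domain and within phase. For the two physiological items, report their inter-item correlation. This is limited evidence in itself: a two-item alpha ranges from 0.18 to 0.67 for inter-item correlations of 0.1 to 0.5.
3. Report stratified alpha for the nine-item total beside ordinary alpha.
4. State that heart rate and saturation will not be judged on their nine-item item-total correlation alone.

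The cost is a few sentences and some extra table rows. No new data are needed, and whole-scale alpha remains available for comparison with other studies.

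### The BPSN–PIPP-R correlation and ROC share two items and the same raters, so part of the agreement arises by construction; overlap-free and cross-rater results should stand beside them

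*Protocol article*

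**What the plan says.** All references are to the protocol article.

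- **Analysis.** Under Data analyses, concurrent validity is assessed as follows: "the total sum scores of the two tools will be correlated". The same paragraph plans a ROC analysis for sensitivity and specificity with the PIPP-R as reference, and a comparison of the two tools' cut-offs.
- **Shared content.** The background section on the scale describes nine BPSN items, including "two physiological (i.e. objective) (changes in heart rate and oxygen saturation) indicators". Under Measures, the PIPP-R "measures five indicators of which two are physiological (heart rate and oxygen saturation". The BPSN values come from the routine monitor during the recording; no separate source is described for the PIPP-R.
- **Shared raters.** Under Recruitment and data collection procedures, five nurses retrieve the randomized sequences and "will rate the behavioral pain reaction by means of the BPSN and the PIPP-R". Measures says of the facial items: "The three behavioral indicators (brow bulge, eye squeeze, and naso-labial furrow) will also be assessed by the five raters". Blinding covers measurement phase and heel-stick number. Nothing is said about keeping one tool's score from the other.
- **Contextual points.** Under Measures, "the PIPP-R accounts for GA and baseline behavioral states as contextual factors". They are scored only if another item changes.
- **Cut-off.** For the BPSN, "a total score of 11 or higher is considered to indicate pain".

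**The concern.** A correlation between two instruments supports validity to the extent that they could have disagreed. Here two signals enter both totals, so they add positive covariance whatever the remaining items do. In the ROC the problem takes the form of incorporation bias: part of the index test sits inside the reference standard. A nurse who scores both tools on one sequence can also carry a single impression into both totals.

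Nothing in the text separates this from true agreement. The sentence about analysing physiological and behavioral items on their own follows the comparison of phase means and comes before the PIPP-R comparison is introduced. The last paragraph of Data analyses relates BPSN subscores to BPSN totals and to each other. Neither takes the common items out of the PIPP-R comparison.

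Concurrent validity, sensitivity and specificity are named study aims, and the results are to inform a modified scale. The Background says that no accepted gold standard exists, so agreement with the PIPP-R has to be interpretable.

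**Working it through.** The article states no expected correlation or AUC, so there is no figure to reproduce. What can be checked is how much agreement the shared items create under stated assumptions.

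**Inputs from the article.** BPSN: 9 items, 7 subjective and 2 physiological. (Measures counts six subjective indicators but lists seven; seven is used here.) PIPP-R: 5 indicators, 3 facial and 2 physiological, plus 2 contextual items. Shared: 2.

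**Assumptions.** Equal item variances (set to 1), a common inter-item correlation r, shared items scored alike in both tools, contextual points ignored.

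**Formulas.**
- Var(BPSN) = 9 + 72r; Var(PIPP-R) = 5 + 20r.
- Covariance with overlap = 45r + 2(1 − r). Of the 45 item pairs, two are an item paired with itself.
- Covariance for equal-length scales without overlap = 45r.
- Seven BPSN-only against three PIPP-R-only items: correlation = 21r / √[(7 + 42r)(3 + 6r)].

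| r | With overlap | Same length, no overlap | Added by overlap | 7 vs 3 items |
|---|---|---|---|---|
| 0 | 2/√45 = 0.30 | 0 | 0.30 | 0 |
| 0.1 | 6.3/√(16.2 × 7) = 0.59 | 4.5/√(16.2 × 7) = 0.42 | 0.17 | 0.33 |
| 0.3 | 14.9/√(30.6 × 11) = 0.81 | 13.5/√(30.6 × 11) = 0.74 | 0.08 | 0.65 |
| 0.5 | 23.5/√(45 × 15) = 0.90 | 22.5/√(45 × 15) = 0.87 | 0.04 | – |

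The overlap effect is the fourth column. The further fall to the last column (0.42 to 0.33; 0.74 to 0.65) comes from shorter scales and is not overlap.

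**Relaxing the assumptions at r = 0.** Counting the two contextual items as PIPP-R components gives 2/√(9 × 7) = 0.25. If the physiological items correlate only 0.7 across the tools, the values are 1.4/√45 = 0.21 and 1.4/√63 = 0.18.

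**Unequal correlations.** Assumed values: 0.3 to 0.5 among BPSN behavioral items, 0.5 to 0.7 among PIPP-R facial items, 0 to 0.5 across tools, 0.2 to 0.3 between the two physiological items, 0 to 0.2 between behavioral and physiological items. The overlap then added 0.07 to 0.12. It added 0.02 to 0.04 when, in addition, the contextual items were counted (and treated like the facial ones) and the shared items correlated 0.7 across tools.

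**ROC.** Simulated 0–3 items, 200,000 observations per scenario, at least about 30% classed as pain by the PIPP-R. With no true association, the shared items alone gave an AUC of 0.64 instead of 0.50. With true signal (item loadings 0.3, 0.5, 0.7; physiological items at 0.6 of these) and no halo, the AUC was 0.73, 0.83 and 0.91 with shared items. With equally long scales measuring physiology separately it was 0.63, 0.76 and 0.87.

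**Halo.** An assumed same-rater loading of 0.4, with no true signal and no shared items, gave r = 0.29 and AUC = 0.64; separate raters gave 0.00 and 0.50. The loading is arbitrary, so this shows direction only.

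**The case against.** Correlating totals with an established tool is a usual step, and the overlap is plain from the article's own description of the tools. The aim is agreement between the instruments as used. The cut-off of 11 belongs to the nine-item total, so a ROC on seven items against three facial items could not assess it or support the planned comparison of cut-offs. All of this stands, and it is why the total-score analyses should stay.

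A reader might infer that the subscore comparison should become primary. The arithmetic does not support that. At r = 0.3 shortening the scales costs about 0.09, more than the overlap adds (0.08), and pairing different raters lowers the coefficient further through rater unreliability. One bias would be exchanged for another. Content overlap would also remain between the BPSN facial-expression item and the three PIPP-R facial items.

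A reader might also infer that the reported coefficient must be too high. Only the sign of the overlap component is established. The PIPP-R gives its highest contextual scores to the youngest infants and to quiet sleep, while the Background describes weaker responses in premature infants; that can pull the correlation down. Scoring those points only when other items change can push it up.

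Halo is plausible but not shown. The article does not say whether both tools are scored in one viewing or whether ratings are averaged. Averaging over five nurses would cut each nurse's independent error variance to one fifth. Blinding to phase limits halo driven by expectation.

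Finally, validity does not rest on the PIPP-R alone. The phase comparison, planned also for the behavioral items by themselves, uses no PIPP-R score. No threshold is set for r or AUC, and the sample size rests on another association. These points lower the weight of the concern. They do not make the PIPP-R comparison itself interpretable.

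**Conclusion.** The point holds in a limited form. The shared signals and shared raters are in the text, the stated analyses keep both, and the shared items add positive covariance. Under the simple model the overlap accounts for r of about 0.30 (0.25 with contextual items counted) when nothing else is related, and it adds about 0.17 at r = 0.1 and 0.08 at r = 0.3. Less favourable but plausible assumptions bring the addition down to a few hundredths. The effect is largest where items are weakly related. The weight falls mainly on the ROC, where the PIPP-R serves as reference.

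All sizes rest on item correlations and scoring identity that the article does not give; they are illustrations, not predictions. The documents do not support the conclusions that the BPSN lacks validity, that the final correlation will be overstated on balance, or that the total-score analyses are wrong to run. They do support this: total-score agreement alone cannot carry the validity, sensitivity and specificity conclusions.

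**What to change.** Keep the total-score correlation and ROC, and pre-specify two analyses beside them:

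- **(a) Cross-rater.** The same correlation and ROC with the BPSN from rater i and the PIPP-R from rater j, i ≠ j, averaged over pairs. This addresses halo but leaves the shared monitor items in.
- **(b) Overlap-free.** A correlation and ROC with heart rate and oxygen saturation removed from both tools. This addresses the overlap but leaves halo in unless it is computed on the pairs of (a), which the same ratings allow.

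Say in advance that shorter scales and rater unreliability attenuate (a) and (b), so that the gap to the total-score result is not read wholly as overlap. State the shared items and raters wherever the PIPP-R comparison is reported, and draw the validity, sensitivity and specificity conclusions from the set of results together.

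The five nurses already score both tools, so no new ratings are needed. The cost is some added analysis and less favourable reported coefficients.
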